#### Sensitivity analysis

In a sensitivity analysis, we extend the follow-up of the composite primary outcome to 120 days after the index event. Secondly, we perform separate analyses for the outcomes death, first-time nursing home care and paid nursing care for the first time, which together make up the composite endpoint in the primary analysis. Thirdly, we perform a subgroup analysis of the composite primary outcome for following groups: patients with stroke vs other defined acute neurological diseases; patients with vs without nursing care before the index event; patients in cooperating hospitals with vs without neurological departments or telemedicine support before the start of the ANNOTeM intervention. Finally, we investigate patients in the cooperating hospitals with traumatic brain injuries who cannot be included in the main intervention group as a companion study population.

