### Study population

#### Inclusion criteria

To determine the composite primary outcome of time to death or first-time care at home or paid care support for the first time within 90 days after the index event, we will use routine data from three cooperating health insurance companies (AOK Nordost, BARMER, TK). For this purpose, eligible study participants must (1) have continuous health insurance with one of these health insurers during the evaluation period, (2) be admitted during the intervention or control period to one of the cooperating regional hospitals, (3) have a neurological diagnosis (International Classification of Diseases (ICD)-10 main diagnosis) such as stroke (I60–64), status epilepticus or impaired level of consciousness (G41, R40), meningitis /encephalitis (A82.0–2, A85–87, G00–03, G06–09), acute spinal cord injury (S14, S24, S34, G82), (4) and be over 18 years of age of both sexes.

We had originally planned to include patients diagnosed with traumatic brain injury (S06–07) in an earliert version of the study protocoll. However, since patients with traumatic brain injury are only rarely managed by our project partners in the participating regional hospitals they are not included in the primary study population, but rather as a companion study population in a sensitivity analysis.

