### Study objectives

#### Primary outcomes

The composite primary composite outcome is time to 1) death, **2)** first-time nursing home care or, 3) paid outpatient nursing care for the first time within 90 days after the index event, whichever occurs first.

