#### Sample size calculation

Sample size was calculated on the assumption that the implementation of the ANNOTeM concept in the cooperating regional hospitals reduces the rate of dependency from 39% in the control period to 32% in the intervention period, i.e. a relative reduction by one fifth. The assumptions are based on the results of the TEMPiS trial [13].

Patient recruitment started in November 2017 and will run to 31 July 2020. According to the annual case numbers, at least 1820 patients per group with defined inclusion criteria are expected in the eleven cooperating regional hospitals during the intervention period. This sample size ensures a power of 80% (corresponding to a beta of 0.20) and an alpha of 5% for a two-sided test. Case size calculation was performed in nQuery Advisor 7.0.

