### Statistical analyses

#### Primary analysis

Because health insurance data will be provided anonymously, we cannot determine the effect of telemedicine consultation on an individual patient level. Rather, we will evaluate the effects of the ANNOTeM concept in clusters. The primary outcome will be analysed as the time from the index visit to the occurrence of the compound outcome as described above. Separate Cox models will be fitted for eligible patients insured at the cooperating health insurance companies, admitted and treated in both, the pre-implementation period and the intervention period. Cox models will comprise sex (m/f only), age and co-morbidity (Y/N) as covariates. Hazard rate ratios will be used to compare time-to-compound event between the two periods. All tests will be performed at a significance level of alpha = 0.05, adjusted for two-sided testing and the k = 6 tests of the primary and secondary analysis. All tests will be performed using the statistics package ‘R’ (version 3.6).

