### Data collection, management, and analysis

#### Data collection methods

The health insurance data for determining the defined outcomes are provided by the cooperating statutory health insurance companies (AOK Nordost, BARMER, TK) in accordance with the defined inclusion criteria. Within the framework of ANNOTeM, pseudonymised personal data of the health insurances will be transmitted in accordance with §75 Social Security Code V to a third trust party, which forwards the data in anonymised form to the evaluating institute. This forwarding has been approved by the supervisory authorities of the participating health insurance companies.

In addition to the account data for identifying the defined outcomes and costs, basic data on age and sex, insurance status and paid nursing care or nursing home care are provided at the beginning of observation.

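### Patients already in nursing care are pooled into a first-time-care endpoint and the primary Cox model omits baseline care status, so a shift in their share between periods can move the hazard ratio either way

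*Protocol article*

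**What the plan says.** All references are to the protocol article.

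- **Endpoint.** Primary outcomes lists death together with "first-time nursing home care or, 3) paid outpatient nursing care for the first time within 90 days after the index event", whichever comes first.
- **Population.** Inclusion criteria names four conditions: continuous insurance, admission to a cooperating hospital in either period, a listed ICD-10 main diagnosis, and age. None concerns care received before admission.
- **Prior care as a subgroup.** Sensitivity analysis plans the composite separately for "patients with vs without nursing care before the index event". Both kinds of patient are therefore in the analysed population.
- **Model.** Under Primary analysis, "Cox models will comprise sex (m/f only), age and co-morbidity (Y/N) as covariates". Baseline care status is not among them.
- **Data.** Data collection methods says that, besides age and sex, "insurance status and paid nursing care or nursing home care are provided at the beginning of observation".

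**The concern.** The endpoint, the population and the covariate list are each stated, and they do not fit together. If first-time care means care never received before, the events open to a patient depend on care status at admission. A care-naive patient can reach all three components. A patient with outpatient care can reach death or nursing home entry. A nursing-home resident is in practice left with death alone. One hazard ratio is then estimated over groups at risk of different events.

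This matters more here than in a randomised trial. The primary contrast is historical: admissions from November 2014 to May 2017 against admissions from November 2017 to July 2020, so nothing balances baseline care between the arms. Table 1 also shows hospitals starting recruitment at dates from November 2017 to February 2019, so the hospital mix may differ between periods. That is one route by which the prior-care share could change; it is not evidence that it did. If the share does change, the composite rate moves although acute care has not.

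**Working it through.** **Inputs from the article.** Control rate 39%, intervention rate 32% (Sample size calculation: "reduces the rate of dependency from 39% in the control period to 32% in the intervention period"); at least 1820 patients per group. The planned effect is 39 − 32 = 7 points, a relative reduction of 7/39 = 17.9%, which matches the stated one fifth approximately.

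**Inputs not in the article, so assumed.** The prior-care share in the control period (q0) and intervention period (q1), and the 90-day composite event rate in prior-care patients (m). The 39% is also assumed to be the care-naive rate; the article does not say to whom it applies.

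**Step 1: shift with no true effect.** The pooled rate in a period is (1 − q) × 39% + q × m. With the same component rates in both periods, control minus intervention is

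(q1 − q0) × (39% − m).

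For a rise of 10 points in the share:

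| m | Calculation | Crude shift |
|---|---|---|
| 15% | 0.10 × (39 − 15) | 2.4 points, apparent benefit |
| 25% | 0.10 × (39 − 25) | 1.4 points, apparent benefit |
| 39% | 0.10 × (39 − 39) | 0 |
| 50% | 0.10 × (39 − 50) | −1.1 points, apparent harm |

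A 5-point rise halves each figure; a fall in the share reverses the signs.

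**Step 2: on the hazard-ratio scale.** Take the share as 20% then 30%, and HR ≈ ln(1 − intervention rate)/ln(1 − control rate).

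- m = 15%: control 0.8 × 39 + 0.2 × 15 = 34.2%, intervention 0.7 × 39 + 0.3 × 15 = 31.8%; HR about 0.91.
- m = 25%: 36.2% and 34.8%; HR about 0.95.
- m = 50%: 41.2% and 42.3%; HR about 1.04.

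With 1820 independent patients per group and an unadjusted two-sided 5% test, the chance of a false positive favouring the intervention is about 34% at m = 15% and 14% at m = 25%.

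**Step 3: dilution.** If the intervention does nothing for prior-care patients, the difference is (1 − q) × 7 points: 6.3 at q = 10%, 5.6 at 20%, 4.9 at 30%. Power with 1820 per group at 5% is then 98%, 94–95% and 87–90% (m from 15% to 35%), and falls below 80% only once q passes about 37–41%. If these patients instead have the same relative effect on death, the difference at q = 30% is 5.7–6.8 points and power is 97–98% or more.

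**The case against.** Four points on the other side carry weight.

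**The prior-care group is not event-free.** A reader might infer that people already in care cannot have an event. The article does not support that: anyone can die, and an outpatient-care recipient can still enter a nursing home for the first time. This brings their rate closer to 39% and reduces the shift. It stands, and it is why m is shown over a range.

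**The direction is unknown.** A reader might infer that a higher prior-care share in the later period must look like benefit. That holds only if m is below the care-naive rate. Moreover, the phrase "paid outpatient nursing care for the first time within 90 days after the index event" could mean the earliest paid care recorded inside the window; patients already in care would then have near-automatic events, and a rising share would look like harm. The article does not settle which reading applies. Either way, the event rule for these patients needs stating.

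**Dilution is conditional.** It requires a smaller effect in prior-care patients, and if the 39% and 32% already refer to all patients, Step 3 counts it twice. This stands: power is not the main issue.

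**Other analyses help in part.** The prior-care subgroups and separate component analyses are planned. The non-network comparison would pick up a region-wide change in case mix. Age and co-morbidity would absorb some of a shift, which the crude figures ignore. But a subgroup analysis does not correct the pooled primary estimate. The non-network comparison is secondary, is described as a log-rank test with no listed adjustment for prior care, and does not cover a shift confined to network hospitals.

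Including all patients is also a legitimate choice for a hospital-level intervention; Discussion counts complete capture of patients as a strength. The article gives no ground for saying that the primary analysis must exclude patients in care.

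**Conclusion.** The point holds as a weakness in how the primary model is fixed. Patients whose possible events differ by baseline care status are pooled in a non-randomised before/after comparison, and the model leaves out the variable that separates them although it is delivered.

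For a 10-point change in share, the crude shift runs from 2.4 points of apparent benefit to 1.1 points of apparent harm, against a planned 7. This assumes a 39% care-naive rate, m between 15% and 50%, and no absorption by the listed covariates. The documents do not show that the share changes, how large it is, or which way any bias runs. The case for a change rests on interpretability and protection against case-mix bias, not on a demonstrated bias or a loss of power.

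**What to change.** 1. Stratify the primary Cox model by care status at the beginning of observation: none, outpatient care, nursing home. Each stratum then has its own baseline hazard, and a change in the strata's shares no longer moves the hazard ratio. The common hazard ratio still averages over different sets of events, so report the stratum estimates beside it.
2. State which components count as events in each stratum, and whether first-time means never before or first within the follow-up window.
3. Report the care-naive analysis, already planned as a subgroup, as a key sensitivity analysis, and tabulate the prior-care share by period.

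The cost is analysis-plan wording. The variable is already supplied and no patients are lost.

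Restricting the primary analysis to care-naive patients is optional. It changes the estimand and leaves 1820 × (1 − q) per group. At 39% against 32%, with independent patients and 5% alpha, power would be 97.7% at q = 20%, 95.9% at 30% and 87.8% at 50%. It would be lower under the planned adjustment for six tests: 90.5%, 85.5% and 68.6% if that means alpha 0.05/6.

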### Data collection, management, and analysis

#### Data collection methods

The health insurance data for determining the defined outcomes are provided by the cooperating statutory health insurance companies (AOK Nordost, BARMER, TK) in accordance with the defined inclusion criteria. Within the framework of ANNOTeM, pseudonymised personal data of the health insurances will be transmitted in accordance with §75 Social Security Code V to a third trust party, which forwards the data in anonymised form to the evaluating institute. This forwarding has been approved by the supervisory authorities of the participating health insurance companies.

In addition to the account data for identifying the defined outcomes and costs, basic data on age and sex, insurance status and paid nursing care or nursing home care are provided at the beginning of observation.

#### Data management

The manual for data management was approved by TMF (Technologies, Methods and Infrastructure for Networked Medical Research) and the data protection officer of the Charité.

## Discussion

Ageing populations along with structural deficits in underserved regions of North-East Germany [17] with an increasing shortage of medical specialists are major challenges in providing state-of-the-art treatment for acute neurological patients. At the same time, there is a need for comprehensive access to new, evidence-based therapies and standardized operating procedures for neurological emergencies in community hospitals, mostly without a neurology department. New initiatives to combine medical expertise with the use of modern infrastructural components have been established within the framework of telemedicine networks. So far, evidence for improving the quality of care is only available from acute telestroke projects. Hence, there is a need for large-scale studies that examine the benefits of such networks for outcomes and cost-effectiveness. ANNOTeM evaluates clinical outcomes for patients with acute neurological diseases including but not exclusively stroke treated with telemedicine support. ANNOTeM aims to establish and sustainably improve regional structures by continuous knowledge transfer to all professional groups involved in the care of acute neurological patients in the regional hospitals by continuous training and the introduction of standardized processes.

We acknowledge several limitations of the study: Changes in the care of patients with effects on the primary outcomes measured here may occur independently of study design through health policy measures and health care innovations. This can result in an overestimate of improved care for the intervention group compared to the pre-implementation control group. In order to control for this possible time trend, we have introduced a parallel control group of patients treated in non-network hospitals. A further limitation is that the definition of part of the composite outcome is based on routine data of the health insurances. It is possible that patients or their relatives do not apply for home care support provided by the health system even when they have a respective need of assistance. In addition, the decision for home care also depends, among other things, on the available social support at home or personal preferences. However, previous analyses have shown that the parameters of care support and home care correlate well with the degree of disability [18]. The approach taken in this project will be evaluated in the setting of the German health care system and results can therefore not be generalized.

On the other side, the study has several important strengths. First, the total number of patients treated in the hospitals with regard to the main diagnoses is recorded on the basis of health insurance data. Thus, the bias of patient selection by informed consent procedures often present in clinical studies is minimized. Second, study outcomes are assessed independently. Third, the combination of data collected within the telemedicine consultations along with quality management of the health insurance data provide the opportunity to evaluate the effects with a direct link to the health care context.

### Study status

The intervention started in November 2017 and results are expected in January 2021.

## Data Availability

Not applicable.

## Abbreviations

AWMF: Joint Workgroup of German Medical Societies (Arbeitsgemeinschaft der Wissenschaftlichen Medizinischen Fachgesellschaften)
CT: Computer tomography
DGN: German Neurological Society (Deutsche Gesellschaft für Neurologie)
GDPR: General Data Protection Regulation
ICD: International classification of diseases
ITT: Intention-to-Treat
MRI: Magnetic resonance tomography
SOP: Standardized operating procedures
TMF: Technologies, Methods and Infrastructure for Networked Medical Research
